### Objectives

#### Primary objectives

Assess the ability to implement MDA-adapted WHO PEN protocols 1 and 2 in pilot primary healthcare centres.Determine the feasibility of collecting quantitative data required for future studies of effectiveness from the existing informal paper clinical record system.

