#### Step 6: collection of follow-up data

After 12 months, using the same method and data collection instruments used to collect baseline quantitative data (step 3), data will again be extracted from randomly selected individual paper-based patient records from all 20 healthcare centres. Five primary healthcare centres from the intervention arm will be selected by the national steering group for one-on-one semi-structured interviews with health staff. This will be supplemented by inviting a selection of staff from all 10 health centres in the intervention arm to participate in focus groups. Together, these qualitative data will be analysed thematically for explanatory themes.

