### Quantitative indicators

Indicators were developed to balance input and process indicators, such as measurement of risk factors and calculation of risk scores, with output (eg, prescribing) and outcome (eg, blood pressure control) indicators. While one of the objectives of this evaluation is to determine the ability to measure these indicators based on routine paper records, we used our existing knowledge of the health system to design indicators which were valuable and likely to be feasible to calculate. Table 1 shows the indicator, the question the indicator seeks to answer and the respective numerator and denominator definitions that will be used in the calculations.

**Table 1 T1:** Indicators, their numerators and denominators and questions the indicators answer

Question	Indicator	Numerator	Denominator
Are risk factors being measured?	Proportion of eligible patients who have all risk factor values recorded as required for calculation of risk score.	Patients aged 40 years or older who have visited in the last 12 months who have all measurements required for calculation of risk score within 12 months of the most recent date of visit.	Patients aged 40 years or older who have visited in the last 12 months.
Are risk factor measurements being converted to a total risk score?	Proportion of patients aged 40 years or older who have visited in the last 12 months who have all measurements required for calculation of risk score within 12 months of the most recent date of visit, which have a documented risk score.	Patients aged 40 years or older who have visited in the last 12 months who have all measurements required for calculation of risk score within 12 months of the most recent date of visit, which have a documented risk score.	Patients aged 40 years or older who have visited in the last 12 months who have all measurements required for calculation of risk score within 12 months of the most recent date of visit.

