Are risk scores calculated correctly?	Proportion of patients aged 40 years or older who have visited in the last 12 months who have all measurements required for calculation of risk score within 12 months of the most recent date of visit, which have a documented risk score that is correct.	Patients aged 40 or older who have visited in the last 12 months who have all measurements required for calculation of risk score within 12 months of the most recent date of visit, which have a documented risk score that is correct.	Patients aged 40 or older who have visited in the last 12 months who have all measurements required for calculation of risk score within 12 months of the most recent date of visit, which have a documented risk score.
Are patients being risk scored?	Proportion of eligible patients with a documented risk score.	Patients aged 40 years or older who have visited in the last 12 months with a documented risk score.	Patients aged 40 years or older who have visited in the last 12 months.
Are risk scores calculated correctly?	Proportion of eligible patients with a documented risk score that is correct.	Patients aged 40 years or older who have visited in the last 12 months with a documented risk score that is correct.	Patients aged 40 years or older who have visited in the last 12 months with a documented risk score.
Are statins prescribed to the correct patients?	Proportion of eligible patients prescribed a statin.	Patients with existing CVD, patients with diabetes aged 40 years or older with high LDL values (as defined based on total CVD risk of SCORE 10%–14% in LDL≥2.6 mmol/L; with very high risk SCORE≥15% in LDL≥1.8 mmol/L), or patients with a SCORE of ≤9% and LDL≥2.6 or total cholesterol≥7.2, or patients with a SCORE of 10%–14% and LDL≥1.8 or total cholesterol≥7.2 mmol/L, or patients with a SCORE of ≥15%, prescribed a statin.	Patients with existing CVD, patients with diabetes aged 40 years or older with high LDL values (as defined based on total CVD risk of SCORE 10%–14% in LDL≥2.6 mmol/L; with very high risk SCORE≥15% in LDL≥1.8 mmol/L), or patients with a SCORE of ≤9% and LDL≥2.6 or total cholesterol≥7.2, or patients with a SCORE of 10%–14% and a LDL≥1.8 or total cholesterol≥7.2 mmol/L, or patients with a SCORE of ≥15%.

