### Data collection and management

#### Quantitative data collection tool

A standardised data collection template has been developed for extracting anonymised patient data from individual paper records (table 2). An online version was also made to allow for data entry on a computer or smartphone. It is estimated to take 15 min to extract data from one patient record since the records are made of blank paper with no formal structure or organisation of health data.

**Table 2 T2:** Standardised data collection form used to extract data from individual patient records

Data collection question	Answer
What is your name? (Name of person extracting data)	
Date of data extraction (MM-DD-YYYY)	
Write the clinic name	
Is this a duplicate extraction?	
If it is a duplicate extraction, enter the number you and your extraction partner have assigned to this file.	
Date of birth (MM-DD-YYYY)	
Sex (M/F)	
Smoking status (Y/M)	
Diagnosis of hypertension (Y/N)	
Date of hypertension diagnosis (MM-DD-YYYY)	
Can you find one or more blood pressure readings? (Y/N)	
Most recent systolic blood pressure	
Most recent diastolic blood pressure	
Date of the most recent blood pressure measurement (MM-DD-YYYY)	
Can you find a second most recent blood pressure reading? (Y/N)	
Second most recent systolic blood pressure	
Second most recent diastolic blood pressure	
Date of the second most recent systolic blood pressure (MM-DD-YYYY)	
Diagnosis of diabetes (type 1, type 2, no)	
Can you find one or more glycated haemoglobin (HbA1c) measurements? (Y/N)	
Most recent HbA1c reading (mmol/mol)	
Date of the most recent HbA1c measurement? (MM-DD-YYYY)	
Can you find another HbA1c measurement? (Y/N)	
Second most recent HbA1c reading (mmol/mol, otherwise specify unit)	
Date of the second most recent HbA1c reading? (MM-DD-YYYY)	
Can you find one or more total cholesterol measurements? (Y/N)	
Most recent total cholesterol reading (mmol/L)	
Date of the most recent cholesterol reading (MM-DD-YYYY)	
Can you find another cholesterol measurement? (Y/N)	
Second most recent cholesterol reading (mmol/L)	
Date of the second most recent cholesterol reading (MM-DD-YYYY)	
Was the patient prescribed a statin? (Y/N)	
What was the date of the statin prescription? (MM-DD-YYYY)	
What was the drug and dose?	
Does the patient have existing cardiovascular disease (CVD)? (Y/N)	
State the type of CVD	
Has the patient been prescribed acetylsalicylic acid (ASA or aspirin)? (Y/N)	

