#### Method of randomly sampling patient records

A random sample of the records of patients aged over 18 years, who have visited the medical facility within the past 12 months, will be taken. Since medical records in MDA are organised alphabetically on shelves, we created a randomly generated list of alphanumeric combinations that allowed for the selection of patient charts at random. For example, an alphanumeric code of ‘C24’ would correspond to the 24th patient chart in the section of last names starting with the letter C.

The list will be followed in the order that it was generated so as to prevent selection bias. The randomly selected chart will then be checked to see if it meets two inclusion criteria^1^: the patient is aged 18 years or older and^2^ the patient visited the health centre within the last 12 months. If the record meets these criteria, data will then be extracted. If it does not, it will be returned to the shelf and the next alphanumeric code on the randomly generated list will be used. This process will be repeated in each clinic until a sample size of 1.2% of the patient population in each clinic is sampled. This proportion was chosen pragmatically such that the average sample per primary healthcare centre would equal 100 unique patients.

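### Statin-eligibility indicator needs LDL, but the extraction form collects only total cholesterol, so it cannot be calculated as defined

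*Protocol article*

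**What the plan says.** Table 1 (section Quantitative indicators) gives the "respective numerator and denominator definitions that will be used in the calculations". In the statin-eligibility row, the numerator is the denominator group restricted to those prescribed a statin. The denominator has five limbs:

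- existing CVD;
- "patients with diabetes aged 40 years or older with high LDL values", where high means LDL of at least 2.6 mmol/L at SCORE 10–14% and at least 1.8 mmol/L at SCORE 15% or above;
- two general limbs below SCORE 15%: "patients with a SCORE of ≤9% and LDL≥2.6 or total cholesterol≥7.2, or patients with a SCORE of 10%–14% and LDL≥1.8 or total cholesterol≥7.2 mmol/L";
- SCORE 15% or above, whatever the lipids.

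Table 2 (section Quantitative data collection tool) is the standardised extraction form. Its lipid value is "Most recent total cholesterol reading (mmol/L"), with a date, a repeat reading and the matching find-it questions. Step 6 says that follow-up data are extracted "using the same method and data collection instruments used to collect baseline quantitative data (step 3"). One of the two primary objectives is to determine the "feasibility of collecting quantitative data required for future studies of effectiveness from the existing informal paper clinical record system".

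**The concern.** The indicator depends on a variable that the instrument does not collect. A statistical analysis plan could not repair this, because the value is never taken from the record.

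Two things are at stake. First, the figure would be labelled as the proportion of eligible patients prescribed a statin, yet it would leave out patients below SCORE 15% whom the row itself makes eligible through LDL. If those patients are treated less often than the ones who remain, the figure overstates coverage. Second, the pilot is meant to learn which data can be obtained from paper records. A blank LDL field would be a finding; a form without the field cannot show how often LDL is recorded.

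**Working it through.** **Form against definition.** Table 2 has 44 items. Six concern lipids: whether a total cholesterol value can be found, the value, its date, and the same three for a second reading. Items for LDL, HDL or triglycerides: 0. The closing notes field is for errors, units and personal notes; it does not ask for LDL.

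**What the form can settle.** Take each limb with LDL unknown:

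| Patient | Status from the form |
|---|---|
| Existing CVD | Eligible |
| SCORE ≥15% | Eligible |
| No CVD, SCORE <15%, total cholesterol ≥7.2 | Eligible |
| No CVD, SCORE <15%, total cholesterol <7.2 | Undetermined; depends on LDL alone |

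Enumerating the rule over CVD, diabetes, age, SCORE, total cholesterol and LDL confirms that the last line is exactly the undetermined set.

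The diabetes limb adds nobody. Diabetes at SCORE 10–14% with LDL ≥2.6 already falls within the general limb for SCORE 10–14% with LDL ≥1.8, and diabetes at SCORE ≥15% qualifies regardless of lipids. The loss comes from the two general limbs.

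**How different the two triggers are (illustration).** The protocol gives one relevant figure, in its introductory section on NCDs as a cause of death: 29.4% of the population has total cholesterol of 5 mmol/L or more. The following are assumptions:

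- normal or log-normal shape, SD 0.9 to 1.3 mmol/L;
- LDL equal to total cholesterol (TC) minus 1.5 to 2.2 mmol/L, so that LDL ≥2.6 corresponds to TC ≥4.1 to 4.8;
- alternatives of 40% and 60% at ≥5, in case clinic attenders have higher values.

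For the normal shape, mean = 5 − z × SD, with z = 0.542 for an upper tail of 0.294. At SD 1.0 the mean is 4.458. Then:

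- P(TC ≥7.2) = P(Z ≥ (7.2 − 4.458)/1.0) = P(Z ≥ 2.742) = 0.31%;
- P(TC ≥4.8) = P(Z ≥ 0.342) = 36.6%;
- P(TC ≥4.1) = P(Z ≥ −0.358) = 64.0%.

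Over all SDs and both shapes:

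| Share with TC ≥5 | P(TC ≥7.2) | P(LDL ≥2.6) |
|---|---|---|
| 29.4% (document) | 0.14–3.4% | 34.5–68.4% |
| 40% (assumed) | 0.35–5.1% | 46.0–79.6% |
| 60% (assumed) | 1.4–9.7% | 65.8–92.3% |

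Within a single distribution, the total cholesterol trigger reaches 0.2–10% as many people as the LDL trigger in the first scenario and 1.6–15% in the third. The limit of 1.8 at SCORE 10–14% would select more than 2.6 does.

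**Effect on the reported proportion.** Gap = share omitted × (statin use in those counted − statin use in those omitted). This is zero if use is equal. Neither factor is given in the protocol, so the gap cannot be quantified.

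**The case against.** The mismatch itself is hard to contest, but its weight can be.

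- **The diabetes limb is redundant.** This is correct. It shows that the row relies on LDL, but it changes no patient's status. It also suggests that the thresholds need a second look, since the row asks a higher LDL of a patient with diabetes at SCORE 10–14% (2.6) than of any patient in that band (1.8).
- **The size rests on stacked assumptions.** Only the 29.4% comes from the protocol. It is a population figure, here applied to patients without CVD and below SCORE 15%. The contrast also presumes that LDL is in the record; the number recoverable is about 35 per 100 multiplied by an unknown share with LDL recorded. This stands, so the figures show an order of magnitude and are not an estimate.
- **The consequence is limited.** One of 14 indicator rows is affected, and the change in indicators serves a secondary objective. The separate rows for statins in existing CVD and for statins at documented SCORE ≥15% do not need LDL. This stands and fixes the severity.
- **This is a pilot, and the interviews could reveal whether LDL is recorded.** This stands only in part. Staff opinion gives no rate of availability, whereas a field on the form would.
- **A condensed article may omit detail.** This does not help. Table 2 is printed as the form itself, down to the extractor's name, and it conflicts with a definition in the same article.

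**Conclusion.** The point holds. The statin-eligibility row cannot be calculated as defined at baseline or follow-up, because the form supplies none of the LDL values that the definition needs. What can be calculated is a narrower indicator: existing CVD, SCORE ≥15%, or total cholesterol ≥7.2.

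Under the stated assumptions, and if LDL were recorded for all, about 0 to 3 (at most about 10) per 100 patients without CVD and below SCORE 15% could be counted as eligible from the form. About 35 or more would be counted under the LDL ≥2.6 limit. The share omitted from the whole row is not estimated, since the proportions with CVD or SCORE ≥15% are not given. No difference between arms or rounds is claimed. Severity is minor.

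**What to change.** **Preferred.** Add the LDL value and its date to Table 2, in all 20 clinics and at both rounds, and calculate the row as defined. Before doing so, confirm the LDL limits for patients with diabetes, given the redundancy above. Do not add LDL at follow-up only: that would widen the denominator at one round and make the change from baseline uninterpretable.

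**If LDL is not collected, or baseline extraction is already done,** split the row:

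1. statin use in existing CVD or SCORE ≥15%, using the calculated score so that undocumented high scores are kept;
2. statin use in patients without CVD and below SCORE 15% with total cholesterol ≥7.2, as a separate line;
3. a statement that the LDL-defined groups below SCORE 15%, including diabetes at SCORE 10–14%, were not assessed. Patients with diabetes at SCORE ≥15% are counted in line 1.

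**Cost.** The protocol says "It is estimated to take 15 min to extract data from one patient record", and the sampling fraction is set so that "the average sample per primary healthcare centre would equal 100 unique patients". On a simple per-item average, 15 min / 44 = 20.5 s. Two items add 41 s per record; over 20 × 100 = 2000 records that is 22.7 extractor-hours per round, or about 1.1 h per clinic. If the form's usual find-it question is included, three items add 61 s, or about 34 h per round. These are rough figures, because most of the 15 minutes probably goes on searching unstructured notes. LDL may often be absent, which would itself be a feasibility result. The split costs only wording, with smaller denominators on each line.

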Are statins prescribed correctly based on documented risk score?	Proportion of patients eligible based on documented risk score prescribed a statin.	Patients with a documented risk score as very high risk SCORE≥15% prescribed a statin.	Patients with a documented risk score as very high risk SCORE≥15%.
Are patients with existing disease, who do not require the calculation of a risk score to prescribe satins, prescribed statins?	Proportion of patients with existing CVD prescribed a statin.	Patients with existing CVD prescribed a statin.	Patients with existing CVD.
Is the blood pressure of high-risk patients controlled?	Proportion of high-risk patients (SCORE≥15% or DM and age over 40 years) whose last two recorded blood pressure measurements were <130/80 mm Hg.	Patients with a true risk score indicating a very high risk (SCORE≥15%) or DM and age over 40 years whose last two documented blood pressure readings were <130/80 mm Hg.	Patients with a true risk score indicating a very high risk (SCORE≥15%) or DM and age over 40 years.
Is the blood pressure of low-risk patients controlled?	Proportion of low-risk patients (SCORE<15%) whose last two recorded blood pressure measurements were <140/90 mm Hg.	Patients with a true risk score indicating <15% whose last two documented blood pressure readings were <140/90 mm Hg.	Patients with a true risk score indicating <15%.
Are patients with existing CVD prescribed basic medications to reduce risk?	Proportion of patients with existing CVD prescribed a statin and aspirin and blood pressure-lowering treatment.	Patients with existing CVD prescribed a statin and aspirin and blood pressure-lowering treatment.	Patients with existing CVD.
Is the blood glucose of patients with diabetes controlled?	Proportion of patients with diabetes with glycaemic control as defined by last two HbA1c measurements.	Patients with type 2 diabetes whose last two HbA1c measurements were below personal target as defined by MDA-adapted WHO PEN protocol 1.	Patients with type 2 diabetes.
Is the blood pressure of patients with hypertension controlled?	Proportion of patients with confirmed hypertension whose systolic blood pressure is <140/90 mm Hg at last two visits.	Patients with confirmed hypertension whose last two blood pressure readings were <140/90 mm Hg.	Patients with confirmed hypertension.

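### Table 1's high-risk and low-risk blood pressure rows overlap for some patients with diabetes, and neither says where existing CVD belongs

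*Protocol article*

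**What the plan says.** The section Quantitative indicators presents Table 1 as the numerators and denominators to be used in the calculations, so these definitions are fixed in the article itself.

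- **High-risk blood pressure row.** Denominator: "Patients with a true risk score indicating a very high risk (SCORE≥15%) or DM and age over 40 years". Success: "whose last two documented blood pressure readings were <130/80 mm Hg".
- **Low-risk blood pressure row.** Denominator: "Patients with a true risk score indicating <15" per cent, with nothing further. Numerator: "Patients with a true risk score indicating <15% whose last two documented blood pressure readings were <140/90 mm Hg".
- **Statin eligibility row.** For patients with diabetes aged 40 or older, a high LDL is "as defined based on total CVD risk of SCORE 10%–14% in LDL≥2.6 mmol/L", with a separate limit at 15% and above. The plan therefore expects some of these patients to score below 15%.
- **Existing CVD.** Neither blood pressure row mentions it. A separate statin row describes patients with existing disease as those "who do not require the calculation of a risk score to prescribe satins" [sic].
- **Scoring rows.** The fourth row is labelled "Proportion of eligible patients with a documented risk score", but its denominator is every attender aged 40 or older in the last 12 months. The second row uses the same group, restricted to those with all the measurements that a score needs. Neither excludes existing CVD.

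**The concern.** Two rows named high-risk and low-risk, with different targets, read as a partition of patients by risk. As defined, they are not one. The plan puts diabetes over 40 into the high-risk row whatever the score, then lets the same patients into the low-risk row if their score is below 15%. The low-risk proportion would then not describe the population that its label promises, and one patient could be both controlled and uncontrolled in the same report. Existing CVD has no stated place, so two analysts could sort these patients differently.

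The scoring rows raise a lesser question. The article describes the strategy as score-directed primary prevention (section Essential interventions to prevent cardiovascular diseases in primary healthcare), and patients with existing CVD are outside primary prevention. If clinics do not score them, they count as failures, and both the level of scoring and its change are diluted by CVD case-mix.

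**Working it through.** There is no plan figure to reproduce. The check on the blood pressure rows is an enumeration of the definitions; the check on the scoring rows is a short formula.

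**1. Membership of the two blood pressure rows as written**

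| Diabetes | Age | True SCORE | High-risk row | Low-risk row |
|---|---|---|---|---|
| No | any | not computable | no | no |
| No | any | <15% | no | yes |
| No | any | ≥15% | yes | no |
| Yes | 40 or younger | as for no diabetes | as above | as above |
| Yes | over 40 | not computable | yes | no |
| Yes | over 40 | <15% | **yes** | **yes** |
| Yes | over 40 | ≥15% | yes | no |

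Exactly one cell lies in both rows: diabetes, over 40, true SCORE below 15%.

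**2. Effect on one patient in that cell.** Take two readings of 134/84. Against 130/80, 134 and 84 are both too high, so the patient is uncontrolled. Against 140/90, both are below the limit, so the patient is controlled.

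**3. Existing CVD.** The table does not use CVD status. A patient with CVD and no diabetes is high-risk with a SCORE of 15% or more, low-risk below that, and in neither row without a computable score.

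**4. Effect on the low-risk proportion.** Let d be the share of the low-risk row that has diabetes and is over 40, x their control rate at 140/90, and y the rate in the rest. The row as written gives d·x + (1−d)·y; without the overlap it gives y. The shift is d·(y−x). The document gives none of d, x or y. As an illustration only, with x = 30% and y = 50%:

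- d = 5%: 49% instead of 50%
- d = 10%: 48%
- d = 20%: 46%

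If x = y, the shift is zero.

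**5. Scoring rows (second and fourth).** Let c be the share with existing CVD in the denominator, p the scoring rate without CVD, and q the rate with CVD. The indicator as written is (1−c)·p + c·q, which falls short of p by c·(p−q). All three values are assumptions. The largest effect, with q = 0 throughout, for p rising from 20% to 80%:

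| c | Before | After | Rise shown | Rise without CVD |
|---|---|---|---|---|
| 10% | 18% | 72% | 54 points | 60 points |
| 20% | 16% | 64% | 48 points | 60 points |
| 30% | 14% | 56% | 42 points | 60 points |

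The rise shrinks by the factor 1−c. If patients with CVD are scored as often as the others (q = p), nothing is lost.

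**6. The other rows on risk factors and scores.** The first row counts recorded measurements, which can be taken in anyone. The third and fifth (correct scores) already require a documented score, so an unscored patient with CVD never enters their denominators.

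**The case against.** **The indicators are separate proportions.** The plan never adds the two blood pressure rows, and the row on confirmed hypertension overlaps both. Overlap alone is therefore no error. This is fair, but that row is not one half of a high/low pair. Here the labels exclude each other while the definitions do not, and the targets differ.

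**The design blunts the effect.** Clinics are randomised, change from baseline is compared between arms, the study is a pilot not sized on power, and testing the indicators is part of its purpose. A stable case-mix offset in level would largely cancel between arms. That stands for the comparison. It does not help the secondary objective of describing baseline performance, which is about levels. Nor does it undo the dilution of a change in the scoring rows. Randomisation is stratified only on the ratio of patients to doctors, and the models adjust only for age and gender, so CVD case-mix is not directly controlled with 10 clinics per arm.

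**Stronger readings that the document does not support.**

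- A reader might infer that all patients with diabetes over 40 are in both rows. Only those with a true SCORE below 15% are.
- A reader might infer that the plan exempts existing CVD from scoring, so that a fully adherent clinic could not reach 100%. The stated exemption covers statin prescribing only, the adapted clinical protocol is not shown, and the ceiling of 1−c needs the unstated assumption that no such patient is scored.
- A reader might size the effects from the Introduction's 23.0% and 12.3%. The first is the share aged 40–69 with a 10-year risk above 30%, including existing CVD; the second is the share of the population with glucose of at least 6.1 mmol/L. Neither is CVD or diabetes prevalence among attenders.

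**Conclusion.** The definitional fault in the blood pressure rows is real. It rests on the text of Table 1 alone: one group of patients meets both denominators at two targets, and patients with existing CVD but no diabetes are sorted by score without the plan saying so. The low-risk indicator therefore contains patients whom the plan itself classes as high-risk. How far this moves the reported proportion cannot be derived from the document.

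The scoring denominators are a secondary point: a poor fit to a primary prevention strategy, not a contradiction. It affects the second and fourth rows only, and only as far as patients with existing CVD are scored less often than others. The factor of up to 1−c assumes that none is scored and that c is 10% to 30%. The matter is worth correcting because the correction is nearly free; it does not threaten the feasibility aims.

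**What to change.** 1. Reconcile the two blood pressure rows so that no patient falls in both, and state which row holds existing CVD, consistent with the adapted protocol. The sponsor settles which target applies to the overlapping group; this review does not choose one.
2. Report the second and fourth rows of Table 1 (documented risk score) among patients without existing CVD, and make the word eligible in the label match the denominator. The first, third and fifth rows need no change on this ground.

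The cost is wording and a line of code. The data collection form (Table 2) already records diabetes type, existing CVD and date of birth, so no new data are needed. The price is a slightly smaller denominator in one of the blood pressure rows, and fewer records in the two scoring rows.

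### The low-risk blood pressure indicator does not exclude patients with diabetes over 40, whom the row above it classes as high-risk

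*Protocol article*

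**What the plan says.** All of this is in the protocol article, mainly Table 1 under Quantitative indicators.

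- **High-risk row, denominator:** "Patients with a true risk score indicating a very high risk (SCORE≥15%) or DM and age over 40 years". The numerator requires the last two readings to be under 130/80: "or DM and age over 40 years whose last two documented blood pressure readings were <130/80 mm Hg".
- **Low-risk row, label:** "Proportion of low-risk patients (SCORE<15%) whose last two recorded blood pressure measurements were <140/90 mm Hg". The numerator is "Patients with a true risk score indicating <15% whose last two documented blood pressure readings were <140/90 mm Hg" and the denominator is "Patients with a true risk score indicating <15" per cent. None of the three mentions diabetes.
- **Status of the definitions:** the text introducing the table says that it gives "the respective numerator and denominator definitions that will be used in the calculations".
- **Patients with diabetes and a SCORE below 15%:** the row on statin eligibility applies a lower SCORE band to them: "patients with diabetes aged 40 years or older with high LDL values (as defined based on total CVD risk of SCORE 10%–14" per cent.
- **Data available:** the extraction form (Table 2, Quantitative data collection tool) has a date-of-birth field and the item "Diagnosis of diabetes (type 1, type 2, no".

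**The concern.** The labels present the two rows as blood pressure control in high-risk and in low-risk patients. One row defines risk by SCORE or by diabetes with age; the other defines it by SCORE alone. A patient with diabetes over 40 and a low SCORE meets both definitions and is judged against two targets.

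The Introduction names stratifying and targeting people at high cardiovascular risk as the central strategy of the package, and these are the only two rows that report blood pressure control by risk group. Suppose a 55-year-old with diabetes and SCORE 6% goes from 150/95 to 135/85 on both readings. The high-risk row does not move and the low-risk row improves, so a gain in a patient the plan calls high-risk is reported as a gain among low-risk patients. Change in performance is a secondary objective, and one primary objective looks ahead to future effectiveness studies, so the definition may be carried forward.

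**Working it through.** **1. Who is in both rows.** The rules were written as logic and applied to SCORE 5, 12, 15 and 20%, diabetes yes or no, and age 35, 40, 41 and 55. The high-risk condition can be read in two ways.

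- Reading A: SCORE ≥15%, or (diabetes and age >40).
- Reading B: (SCORE ≥15% or diabetes), and age >40.

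Under both readings the same profiles fall in both denominators: diabetes, age 41 or 55, SCORE 5% or 12%. No other profile does. The statin row shows that the plan expects such patients to exist.

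**2. How they are scored.** Taking both readings at the value shown:

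| Both readings | High-risk row (<130/80) | Low-risk row (<140/90) |
|---|---|---|
| 125/75, 129/79 | controlled | controlled |
| 130/80, 135/85, 139/89, 128/85 | not controlled | controlled |
| 140/90 | not controlled | not controlled |

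The rows disagree when both readings are below 140/90 but at least one is not below 130/80. The reverse disagreement cannot occur.

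**3. How much of the low-risk row is affected.** The documents give neither the diabetes share nor the SCORE distribution, so these inputs are assumptions: diabetes share d = 8–20% (all taken as over 40); P(SCORE ≥15%) without diabetes h = 5–15%; with diabetes hd = 1.5h; completeness of SCORE inputs unrelated to diabetes.

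Share of low-risk row with diabetes = d(1−hd) / [d(1−hd) + (1−d)(1−h)]

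- Central case, d = 0.15, h = 0.10: 0.1275 / (0.1275 + 0.765) = 0.143.
- Lowest, d = 0.08, h = 0.15: 0.062 / (0.062 + 0.782) = 0.073.
- Highest, d = 0.20, h = 0.05: 0.185 / (0.185 + 0.76) = 0.196.

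If m is this share, the reported rate differs from the rate in patients without diabetes by m times the difference in control between the two groups. That is about 0.07 to 0.20 points for each point of difference.

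**4. How much of the high-risk row is also in the low-risk row.** Patients with diabetes enter the high-risk row even without a calculable SCORE, but cannot then enter the low-risk row. With c the share with complete SCORE inputs:

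Overlap = dc(1−hd) / [d + (1−d)hc]

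- At c = 1 the grid runs from 0.062 / 0.218 = 0.28 to 0.185 / 0.24 = 0.77; the central case is 0.1275 / 0.235 = 0.54.
- Central case at c = 0.5: 0.06375 / 0.1925 = 0.33.
- Central case at c = 0.2: 0.0255 / 0.167 = 0.15.

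**5. Patients per clinic, as illustration only.** The average sample is 100 records. If 5–15 of these are in the overlap and 20–40% of those fall in the disagreeing band, 5 × 0.2 = 1 to 15 × 0.4 = 6 patients per clinic are scored in opposite ways.

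**6. After the exclusion.** Removing patients with diabetes over 40 from the low-risk row empties the overlap. Under reading A, every patient with a true SCORE is then in exactly one row.

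**The case against.** The case against is mainly about consequence, and much of it stands.

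- **No contrast between the rows is planned.** The Data analysis section compares each indicator between arms and between baseline and follow-up. A reader might infer that a test of risk-targeted care, high-risk row against low-risk row, is compromised. The protocol contains no such test.
- **No bias between arms follows.** The same definition applies in both arms and at both time points. A reader might suspect a distorted treatment comparison; the overlap does not in itself produce one.
- **The overlap with the high-risk row is easily overstated.** The range of 28–77% requires complete SCORE inputs. Whether such data can be found in unstructured paper records is one of the things the pilot is testing.
- **A change in diabetes care need not move both rows.** It may move either or both, depending on which threshold is crossed.
- **Other rows in Table 1 overlap too.** The confirmed-hypertension row uses <140/90 with no exclusion, so a hypertensive patient can still be scored differently there and in the high-risk row. That row asks a different question and carries no risk label, so its overlap misnames nobody.
- **The primary objectives do not depend on this row.** They concern implementation and the feasibility of data collection, and the extracted fields allow either version to be computed later.

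The definition itself remains at fault. The low-risk row is named by risk group, and it includes patients whom the row above names as high-risk. Nor is this a detail left to an analysis plan, because the table states the definitions to be used in the calculations.

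**Conclusion.** The point holds as a misclassification in a secondary indicator. It affects the level of the low-risk figure and how it is read. That patients with diabetes over 40 and SCORE below 15% enter both rows follows from the wording and needs no outside number.

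The size is unknown from the documents. Under the stated assumptions about 7–20% of the low-risk row would have diabetes, so 80–93% of it would be as labelled. The share of the high-risk row that is also in the low-risk row is at most 28–77% and falls as SCORE inputs become less complete. The documents support neither a biased comparison of arms nor a damaged planned contrast. Which blood pressure target suits these patients is a clinical question and is not judged here.

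**What to change.** Reconcile the two rows with the table's own classification. In the low-risk row, add to the label, the numerator and the denominator the clause *and not (diabetes and age over 40 years)*. Leave both blood pressure targets as they are. It would help to bracket the high-risk condition in the same edit, so that it is clear whether the age limit applies to diabetes only.

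The cost is one clause in one table row and a slightly smaller low-risk denominator. No new data are needed, since diabetes status and date of birth are already extracted. The confirmed-hypertension row needs no change.
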